## Abstract

**Background:**

Cardiac rehabilitation (CR) services aim to improve heart disease patients’ health and quality of life and reduce the risk of further cardiac events. Depression and anxiety are common among CR patients but psychological treatments have usually had small effects. In contrast, the recent NIHR-funded PATHWAY trial found that group Metacognitive Therapy (MCT) was associated with improvements in anxiety and depression when added to CR and was more effective than usual CR alone. The next stage is to test implementation of MCT within the National Health Service through the creation of a network of CR beacon sites. The study will test the quality of data capture following addition of a new MCT data-field to the national audit of cardiac rehabilitation (NACR), examine level of adoption at sites, examine mental health outcomes benchmarked against usual CR and the PATHWAY data, examine the enablers and barriers to implementation and the expected resource requirements. The study has been registered: NCT05956912 (13th July, 2023).

**Methods:**

Beacon sites will be recruited as preliminary adopters of group MCT from NHS CR services in England. A national invitation for expressions of interest from CR services will be issued and those meeting eligibility criteria will be considered for inclusion. Two staff at each site will receive training in MCT, and mixed-methods will be used to address questions concerning the quality of patient data recorded, level of adoption at sites, the characteristics of patients attending MCT, the impact of adding MCT to CR on mental health outcomes, and patient, healthcare staff and commissioner views of barriers/enablers to implementation. Exploration of implementation will be informed by Normalisation Process Theory.

**Discussion:**

The study will support development of an NHS roll-out strategy, assess the mental health outcomes associated with MCT, examine treatment fidelity in real-world settings, and evaluate revised data collection structures that can be used to assess the impact of national-level implementation.

**Trial Registration:**

NCT05956912; 13^th^ July 2023.

## Background

Cardiovascular disease (CVD) is the most common non-communicable disease and the largest contributor to morbidity and mortality worldwide (1, 2). Cardiac rehabilitation (CR) programmes aim to facilitate recovery after a heart event, promote healthy behaviours, improve lifestyle risk factors, reduce the risk of further related problems, and improve patients' emotional well-being (e.g., anxiety, depression) and health-related quality of life.

The psychological burden of CVD is well known (2–5). Anxiety and depression are common, affecting approximately 30% of CVD patients (6), and are associated with decreased treatment adherence, poor lifestyle factors (e.g., smoking), poorer quality of life, higher healthcare costs and readmission, increased risk of mortality, and poorer long-term psychological adjustment (2–13). The European Association of Preventive Cardiology has emphasised that symptoms of anxiety and depression in heart disease patients affect the success of CR programmes (14). A recent UK-based study of depression in patients attending CR in the pre and post Covid era reaffirmed the need to prioritise psychological well-being (15). As such, it is imperative to identify and treat symptoms of anxiety and depression effectively to ensure that CR programmes have better clinical outcomes, improve the quality of life of heart disease patients and reduce health service costs.

The effect of interventions to treat anxiety and depression (e.g., pharmacotherapy, psychological therapies) in CVD have produced mixed and often small effects (16–21). The most recent Cochrane review (20) and meta-analysis included 35 randomised controlled trials of 10,703 people with CVD treated for anxiety and depression compared to usual care. Psychological treatments included relaxation techniques, emotional support or client-led discussion, cognitive challenging or cognitive restructuring techniques, and other psychological approaches (i.e., stress management/psychotherapy). There was evidence of small reductions in anxiety (pooled SMD −0.24, 95% CI: −0.09 to −0.38) and depression (pooled SMD −0.27, 95% CI: −0.15 to −0.39) at a median follow-up of 12 months in favour of the intervention. However, insufficient evidence quality means considerable uncertainty about the observed effects exists.

Recently, the National Institute for Health and Care Research (NIHR) funded the PATHWAY Trial (RP-PG-1211-20011) to evaluate for the first-time group metacognitive therapy (MCT) for anxiety and depression in cardiac rehabilitation. MCT is based on a psychological model where anxiety and depression are maintained by common factors, including negative repetitive thinking (i.e., worry, rumination) and threat monitoring. Group MCT is a manualised treatment approach that may be particularly suited to addressing these factors in CR patients. Unlike other therapies, MCT does not require an in-depth analysis and challenging of the content of patients' worries, that in the CR context are often realistic (22, 23). Instead, it focuses on enabling patients to effectively regulate worry, rumination, and other unhelpful behaviours that maintain anxiety and depression. A pilot feasibility trial to assess the acceptability and feasibility of adding group MCT to CR (24) found that adding group MCT to CR did not reduce attendance at routine CR, with 78% of patients attending group MCT. A full-scale randomised controlled trial that followed demonstrated that adding MCT to CR was associated with improved mental health outcomes beyond those obtained in usual care, with lower anxiety and depression (total HADS) at 4-month follow-up [SMD = 0.52 (0.29–0.75), *p* < 0.011], which was maintained at twelve-months [SMD = 0.33 (0.10–0.57), *p* = 0.01]. An incidental finding was that MCT also appeared to reduce the risk of psychological deterioration (25).

In view of these results and the identified need to improve psychological outcomes in cardiac patients, the next step involves evaluating implementation and possible roll-out of group MCT across CR services in the UK National Health Service (NHS). There are multiple challenges to developing and successfully implementing new treatments in practice. Challenges include training a workforce to effectively deliver complex interventions, facilitating patient knowledge and uptake, and ensuring treatment quality, engagement, and participation of stakeholders.

The implementation methodology used in this study is informed by Normalisation Process Theory [NPT; (26)]. NPT (27–31) concerns three core factors and the processes underpinning them: Implementation (introducing an intervention into action), embedding (routine incorporation of an intervention into the everyday work of individuals and groups), and integration (reproduction and sustainability of the intervention in organisations and institutions). NPT focuses on the work that individuals and groups do to enable an intervention to become normalised. Four main components to NPT provide a framework for understanding the factors that facilitate and inhibit implementation: (1) coherence building (sense making), understanding what makes an intervention meaningful; (2) cognitive participation (or engagement), which forms commitment around an intervention (e.g., How do individuals collaborate to establish engagement networks and communities of practice around the intervention?); (3) collective action, understanding how individuals work together to enact the intervention; and (4) reflexive monitoring, which concerns how interventions and their components are appraised.

The initial objectives are to establish and develop a network of NHS beacon sites offering group MCT and to revise and pilot national data monitoring to capture group MCT outcomes.

To facilitate and evaluate implementation quantitative and qualitative methods will be used to address specific questions:
1)What is the quality of data capture and monitoring for group MCT?2)What is the level of adoption of group MCT at each Beacon site and across all sites combined?3)How do patients attending MCT + CR differ from those participating in CR only in terms of sociodemographic and health characteristics?4)What impact does adding group MCT to CR have on mental health and quality of life outcomes benchmarked against CR alone and against the outcomes for MCT plus CR in the PATHWAY trial?5)What are CR staff's views of group MCT training and delivery, and what are the facilitators and barriers?6)What is the acceptability and feasibility of roll-out at the commissioner level, and what are the facilitators or barriers?7)What are the expected and unexpected consequences of implementing group MCT, for example, on existing CR services, staffing needs, administration, and resource requirements?

## Methods

### Study overview

The study will establish “beacon sites” that will provide a network for wider-scale evaluation of roll-out in the NHS. Two therapists will be trained to deliver group MCT alongside CR at each of the participating sites.

A new data-field in National Audit of Cardiac Rehabilitation (NACR) database will be created to aid with data collection on the adoption of group MCT in CR. Routine Hospital Anxiety and Depression Scale (HADS) (32) data will be collected via the NACR database, which routinely contains HADS on patients pre- and post-CR.

Semi-structured interviews will be conducted with CR staff trained in MCT and CR stakeholders to assess the implementation of group MCT within CR services.

Our success criteria are:
1)Establishment of a minimum of three new beacon sites willing and able to support a large-scale roll-out study.2)Addition of an MCT field in the National Audit of Cardiac Rehabilitation (NACR) audit system and preliminary data on the quality of capturing group MCT related outcomes.3)Uptake of group MCT within services at each site will be based on delivering at least two six-session group MCT courses with 3–10 patients per group, with at least 60% attending at least four sessions.4)Identification of barriers and facilitators to implementation in the NHS in the areas of: - how is the intervention understood - how can it be translated into practice - how will it fit into services - how will it be sustained.

### Site recruitment

At least three new Beacon sites, not previously involved in the PATHWAY trial, will be recruited as preliminary adopters of group MCT from NHS CR services in England. Previous sites involved in the PATHWAY trial will also be invited to continue their involvement with MCT-PATHWAY. In addition, we will recruit new CR services. UK CR services will be invited to express an interest in taking part in the adoption study, and express an interest by completing an expression of interest form. CR services who express an interest will be reviewed to assess if they meet the eligibility criteria, and those meeting the eligibility criteria will be invited to participate. The sites will be chosen based on the level of CR referrals and the flexibility of CR staff to engage in at least three days of training to deliver the intervention.

To be eligible, the sites must be:
1)NACR registered and achieved minimum of current amber status on the National Certification Programme for CR (NCP_CR) which is jointly run by the NACR and the British Association for Cardiovascular Prevention and Rehabilitation (BACPR)2)Agree to deliver group MCT to a minimum of two groups (including the pilot therapy group as part of training).3)Release two CR staff for three days of online training, deliver two groups (six sessions × 90 min per group) and take half a day to participate in qualitative interviews.4)CR services must not be participating in any other service evaluations.

### Participants

Beacons sites must identify CR staff members to be trained to deliver MCT. Eligible staff must be healthcare professionals working with cardiac rehabilitation services. All CR staff trained in group MCT will be invited to participate in the interviews; before, during and after MCT training. Post-training interviews will provide a reflective approach to implementation and experience in the delivery of MCT.

In addition to interviewing staff trained in MCT, a range of stakeholders (i.e., CR managers, commissioners) will be invited to take part in qualitative interviews. To be eligible to participate in semi-structured interviews, staff must be a healthcare professional working with cardiac rehabilitation or a professional working at the commissioner level. CR stakeholders will be invited to participate in an interview and recruited from CR services, commissioning groups and other relevant CR stakeholder areas.

### Implementation

Designated CR practitioners at each site will attend three days of online training sessions delivered by the study team at Greater Manchester Mental Health NHS Foundation Trust. Training will be led by AW, the developer of MCT. The training programme will include didactic teaching, watching MCT training videos and role plays, studying the intervention manual, and conducting a pilot therapy group. The first two training days will precede the implementation of the pilot training group. The third training day will follow the pilot group to review any challenges and conduct further training. A detailed treatment manual developed in the previously funded NIHR PATHWAY trial will guide CR professionals in delivering group MCT.

### Group MCT patient eligibility

All patients attending CR who meet the NICE recommendations for acute coronary syndrome (NG185) (33) and heart failure (NG106) (34) will be offered group MCT as part of routine CR. Patients will be invited to participate in group MCT during their assessment appointment. CR practitioners were provided guidance from the research team on how to offer group-MCT to interested and eligible CR patients. In addition, interested and eligible participants will be offered an information booklet on group-MCT which was co-created by the study patient and public involvement group. A minimum of three participants will be required to conduct group MCT with a maximum of 10 participants per group. Participants interested in participating in group MCT will be provided with the dates and times of the sessions. Group MCT will run in six-week blocks alongside CR.

### Intervention

Group MCT is a brief group-based psychological treatment to reduce anxiety and depression symptoms in patients attending CR. The intervention is evidence-based and supported by a structured treatment manual. The intervention consists of six sessions of approximately 90 min and will be delivered face-to-face. It presents a series of structured group exercises to explore and modify thinking patterns and behaviours that keep anxiety and depression going. The treatment approach identifies a pattern of excessive thinking in the form of worry, rumination, and focusing on threats that maintain anxiety and depression and interferes with adjustment to stressful situations. Group MCT aims to reduce this pattern by mapping out and modifying underlying psychological factors (metacognition) involved in regulating thinking. For further details on the intervention and its effectiveness, see Wells et al. (22).

### Data collection

We will add a rehabilitation delivery data field to the NACR database to include uptake of group MCT. In addition, routine outcomes from the NACR database will be collected, including anxiety and depression outcome data (i.e., the Hospital Anxiety and Depression scale), quality of life (i.e., Dartmouth Co-op), and clinical and demographic characteristics. Data will be captured from sites on attendance rates. In addition, CR staff will be asked to complete an adherence checklist to monitor adherence to the treatment protocol.

Qualitative data will be collected through semi-structured interviews completed either face-to-face, via Microsoft Teams, or by telephone. Interviews will follow a topic guide and will be audio recorded, anonymised, and transcribed verbatim. The interviews will be conducted with approximately 10 CR staff members trained in group MCT and 10 CR stakeholders (CR nurses, physiotherapists, occupational therapists, managers, and commissioners).

Participants will be prompted about their perspectives across four domains based on NPT, which include: sense-making (how the intervention is understood and compared with existing practices), implementation (how it is translated into practice), embedding (how will it fit routinely within services), and integration (how will it be sustained as part of routine practice).

### Clinical outcome measures

The Hospital Anxiety and depression Scale [HADS (32)] is a 14-item self-report questionnaire that measures symptoms of anxiety (7 items) and depression (7 items). Items are rated using a 4-point (0–3) scale, with higher scores indicating elevated distress. Scores for each subscale range from 0 to 21 and can be categorised as normal (0–7), mild (8–10), moderate (11–14), or severe (15–21). The NACR pays an annual licence fee for HADS so that all NHS based CR programmes can use it free of charge.

The Dartmouth COOP (35) is a self-report measure designed to evaluate the functional abilities of medical patients. It consists of nine items covering various areas such as physical function, daily activities, pain, social activities, social support, emotions, overall health, changes in health, and quality of life. Each chart includes text and illustrations to assist the user in responding. The responses are graded on an ordinal scale of 1–5, with one being the best score.

### Implementation outcomes

Successful adoption of group MCT at each site is set a-priori as the delivery of two, 6-session group MCT courses with three to ten patients per group, with at least 60% attending a minimum of four sessions. Attendance of a minimum of four sessions was selected as this has previously been defined as the minimum treatment dose (36).

A traffic-light criteria will be used to determine successful adoption.
1.Green – achieved all of the following: (a) Delivered two 6-session group MCT courses, with (b) at least three patients per group, and (c) with a combined total of at least 60% attending four or more sessions.2.Amber - achieved one of the three criteria given above.3.Red - achieved none of the criteria.A green rating indicates that a site has fully met the criteria for successful adoption. Amber is considered partial adoption, where amendments to procedures and protocols might lead to successful adoption. At amber sites, specific qualitative work will be undertaken to understand the reasons for not meeting criteria more fully and to help develop strategies to ameliorate this. Red indicates a failure to meet the requirements.

Semi-structured interviews will be conducted with CR staff trained in MCT and CR stakeholders to assess the implementation of group MCT within CR services. In-depth interviews will follow a topic guide to identify the facilitators and barriers to implementation amongst service users, staff, and commissioners, which was developed and guided by the NPT framework. Data from these activities will be used to determine the mechanisms and processes required to support the adoption of training and implementation. In addition, semi-structured interviews will be conducted with CR staff training in and delivering MCT to assess their view on training and delivery.

### Data analysis

#### Quantitative analysis

The Beacon sites and the NACR database will record patient attendance at group MCT. To assess if the modification to the NACR database successfully captures MCT attendance, descriptive statistics will be used to compare the data on patient attendance collected at the site level with that recorded in the NACR dataset.

To assess implementation of MCT at CR services an overall assessment will be made considering the traffic-light ratings of all beacon sites.

The NACR dataset collects a range of demographic, clinical, functional, and physiological measures on each CR patient, at both entry into CR and at discharge. The NACR data at entry will be used to describe the cohort of patients attending MCT and to compare their baseline characteristics to patients on CR only. The NACR data collected at discharge will be used to compare patient outcomes (HADS and Dartmouth Co-op etc.) between the cohorts (MCT + CR vs. CR alone). The analysis will control for a pre-specified set of baseline (entry) confounders: site, HADS, sex, age, number of comorbidities and number of previous different cardiovascular events. Sensitivity analysis will control for additional covariates that differed between the groups (MCT + CR vs. CR alone) above a specified threshold at entry. Further analysis will adjust for missing outcome scores at discharge. Caution will be exercised when interpreting the results as patients have not been randomised to groups hence systematic differences may exist due to unmeasured confounding factors. Therapist adherence to the MCT manual will be assessed using a checklist recording the treatment components implemented in each session, if any components had been missed, and if so, why. The list includes six to eight items for each session, covering the main techniques administered in each session. Session adherence scores will be computed by counting the total elements completed. Descriptive statistics will be used to assess adherence to the group MCT manual across Beacon sites. In addition, change in adherence over time will be compared between sites.

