## Discussion

MCT is a psychological intervention that has the potential to significantly improve psychological outcomes in patients with CVD and offer added choice and value over standard healthcare practices. The mental health benefits would be substantial if MCT could be provided to the 90,000 patients in the United Kingdom commencing CR annually. However, there are significant recognized challenges to implementing and rolling out complex interventions of this kind. We propose a study that will allow us to create the data-monitoring structure and knowledgebase across beacon sites and evaluate data quality and the real-world effects of implementing MCT. The findings will allow us to adapt and modify data capture and monitoring and better understand group MCT training and delivery to facilitate its implementation in cardiac rehabilitation services. The use of quantitative and qualitative methods will generate data to inform and prepare for potential roll-out and evaluation across CR services in the NHS.

Our quantitative work will provide data on the quality of data-capture, the level of adoption at NHS sites, adherence to the treatment protocol and sociodemographic and heath differences between patients who take-up MCT and those who do not. It will assess performance on key outcomes benchmarked against treatment as usual; however, these results must be interpreted with caution: there will be no randomisation hence estimated group differences – even after control for known factors – will be subject to unmeasured confounding. The qualitative stream will develop an account of the influences on training and barriers and facilitators to implementation that has implications for maximising engagement. Use of the NPT framework will facilitate examination of the factors important for embedding MCT within existing services.

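### The CR-only outcome comparator is not limited to patients who were eligible for MCT, and with site adjustment the contrast rests on takers versus a mixed group at the same beacon sites

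*Protocol article*

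**What the plan says.** All references are to the protocol article.

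- **Offer.** Under Group MCT patient eligibility, CR patients who meet the NICE recommendations for acute coronary syndrome or heart failure "will be offered group MCT as part of routine CR". Entry into the MCT group is then by interest: "Participants interested in participating in group MCT will be provided with the dates and times of the sessions".
- **Exposure and comparator.** Under Quantitative analysis, entry data are used to "describe the cohort of patients attending MCT" and to "compare their baseline characteristics to patients on CR only". Discharge HADS and Dartmouth COOP are then compared between the same two cohorts, MCT + CR and CR alone. Exposure is attendance, not offer.
- **Adjustment.** The pre-specified set is "site, HADS, sex, age, number of comorbidities and number of previous different cardiovascular events". A sensitivity analysis adds covariates that differ between the groups at entry by more than a threshold.
- **How the groups are described.** The Discussion speaks of "patients who take-up MCT and those who do not".
- **Caveat.** Quantitative analysis and the Discussion both warn of unmeasured confounding. The Discussion says it remains "even after control for known factors". Neither names the take-up decision as its source.

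**The concern.** Eligibility for MCT is set by diagnosis, but nothing in the stated outcome comparison applies that rule to the comparator. A CR-only patient may have been offered MCT and not taken it up, or may never have qualified. These are different people for different reasons. The adjustment set would not separate them, because a count of previous cardiovascular events is not an index diagnosis.

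Adjusting for site has a further consequence. At a site without MCT every patient is unexposed, so with site fixed effects such patients do not inform the MCT contrast. A large national CR-only group would look reassuring but would leave the estimate resting on beacon sites.

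The estimate answers research question 4 (MCT plus CR benchmarked against CR alone and against PATHWAY) and will be read when roll-out is discussed. A bias that a simple cohort restriction can remove should not be left to a general caution.

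**Working it through.** The protocol gives no sample size, effect size or power for this comparison, so there is no stated figure to reproduce.

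**1. What restriction removes.** Let *a*, *b* and *c* be the adjusted mean discharge scores without MCT of takers, eligible non-takers and ineligible patients at the same sites. Let *q* be the ineligible share of the CR-only cohort and *E* the true effect.

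- Comparator as stated: mean = (1 − *q*)*b* + *qc*, so contrast = *E* + (*a* − *b*) + *q*(*b* − *c*).
- Comparator restricted to eligible patients: contrast = *E* + (*a* − *b*).

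Restriction removes *q*(*b* − *c*) and leaves the self-selection term (*a* − *b*). The documents give none of *q*, *a*, *b* or *c*, so neither size nor sign can be stated.

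**2. What a pre-offer comparator removes.** Let *p* be uptake among eligible patients. If pre-offer eligible patients resemble the later eligible group as a whole, their mean is *pa* + (1 − *p*)*b*. Then takers minus pre-offer patients = *E* + (1 − *p*)(*a* − *b*). Self-selection shrinks only by the fraction *p*.

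**3. How large *p* could be.** Each site commits to at least two groups (Site recruitment) of 3–10 patients (Group MCT patient eligibility). At that minimum, 2 × 3 = 6 to 2 × 10 = 20 patients per site, or 18 to 60 over three new sites. The numbers eligible per site below are assumptions.

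| Eligible per site (assumed) | Largest *p* with two full groups | Self-selection left, 1 − *p* |
|---|---|---|
| 50 | 20/50 = 40% | 60% |
| 100 | 20% | 80% |
| 200 | 10% | 90% |
| 400 | 5% | 95% |

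The same limits on places mean that many eligible non-takers need not have refused.

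**4. Illustrative simulation.** Every parameter is assumed: 3 beacon and 20 other sites, 150 eligible patients each, half of them before MCT starts, an unmeasured trait that raises both uptake and improvement, a true effect of −2.0 HADS points, and 400 repetitions. All simulated patients are eligible, so it tests the site and self-selection arguments and not step 1.

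| Comparison | Mean estimate | SD |
|---|---|---|
| Takers vs concurrent same-site non-takers, site fixed effects | −3.27 | 0.72 |
| Same, plus non-beacon patients, site fixed effects | −3.28 | 0.72 |
| First row, plus same-site pre-offer patients | −3.10 | 0.65 |
| Takers vs non-beacon patients, no site terms | −3.01 | 0.88 |
| Offer-level: before/after, beacon vs non-beacon, scaled by uptake | −1.80 | 1.99 |

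Non-beacon patients change nothing once site is a fixed effect (−3.27 vs −3.28). Adding pre-offer patients lowers the bias from 1.27 to 1.10, a fall of 0.17/1.27 = 13%. Step 2 predicts about this: uptake under the assumed model is about 22%, and pooling pre-offer with concurrent non-takers gives a reduction of *p*/(2 − *p*) = 0.22/1.78 = 12%. The offer-level estimate comes near the truth, but its SD is nearly three times that of the first row (1.99/0.72 = 2.8).

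**The case against.** **Cohort details may sit elsewhere.** The article does not say which sites or dates supply the CR-only patients, and such details may be in the full protocol or analysis plan. This stands: silence on sites and dates is not held against the plan. The point rests on four things the article does state: the offer rule, exposure by attendance, the comparator's label and the adjustment set.

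**The wording quoted serves another question.** The baseline comparison, and the Discussion's contrast of takers with non-takers, answer research question 3, for which non-takers are a fair comparator. This also stands. But the outcome comparison uses the same two cohorts, with no restriction added.

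**The threshold-based sensitivity analysis could bring in diagnosis.** It could, if diagnosis is recorded and differs enough. That would leave the main analysis unchanged and depends on the data.

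**Site may not be a fixed effect.** No model form is given. With random site effects, non-beacon patients would contribute some information, so the site argument is conditional.

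**The limitation is disclosed, and no success criterion depends on a HADS effect.** Both are true and limit the weight of the point. Disclosure does not remove a bias that a restriction would.

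**Stronger readings.** A reader might infer that the comparator is essentially people who refused MCT. The documents do not support that: places are limited, sessions run on set dates in six-week blocks, and earlier same-site patients are not excluded. A reader might also infer that this is the most confounded contrast available. That is not shown: in the simulation, the other comparisons based on takers were nearly as biased (−3.10 and −3.01 against −2.0).

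**Conclusion.** The concern holds in a limited form. As stated, the outcome comparison sets patients selected by diagnosis and interest against CR-only patients selected by neither rule, and index diagnosis is not in the main adjustment. With site as a fixed effect, the contrast is between takers and a mix of eligible non-takers and ineligible patients at beacon sites.

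The avoidable component is *q*(*b* − *c*). It is zero if nearly all CR patients at beacon sites are eligible, or if ineligible patients have the same adjusted outcomes as eligible non-takers. The article's references to eligible patients imply that some are not, but give no share. Because the sign is unknown, restriction could move the estimate either way. What it secures is a comparator drawn from the population to which MCT was offered.

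Self-selection on interest is not removed by restriction, and a pre-offer comparator for attenders reduces it only modestly. It should be named as the main remaining threat. The conclusion assumes fixed site effects for the statement about non-beacon sites, and that NACR records enough diagnostic detail to apply the eligibility rule. The article mentions clinical measures but does not list the fields.

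**What to change.** 1. **Main outcome analysis:** restrict the CR-only cohort to patients meeting the same acute coronary syndrome or heart-failure eligibility as MCT. This costs only a somewhat smaller comparator.
2. **Caveat:** state that patients enter the MCT group by interest and availability, and that the listed covariates do not capture this.
3. **Sensitivity analysis:** add eligible patients at the same sites who entered CR before MCT was first offered, with a calendar-time term. Preferably compare everyone eligible after the offer with everyone eligible before it, whether or not they attended. At offer level, time and offer can be separated only through an assumed trend, different start dates across sites, or eligible patients at non-beacon sites, so say which is used.
4. **Former PATHWAY sites:** these may continue in the study, so exclude earlier MCT recipients from their pre-offer group.
5. **Reporting:** show concurrent eligible non-takers as a separate group.

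The cost is a wider NACR extract and one or two more models. The pre-offer comparison may carry calendar-time differences, and the offer-level estimate will be imprecise, so both belong beside the main analysis and should not replace it.
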